# 12. Statistical analyses plan

Baseline characteristics and outcomes of the patients in the groups will be compared individually. The primary exposure variable is allocation to the intervention group compared to control group. Categorical variables will be presented as numbers (frequencies) and compared with the Chi-Squared or the Fisher’s exact test, as appropriate, whereas continuous variables will be presented as mean ±SD if normally distributed, and as median (25^th^ percentile-75^th^ percentile) if non-normally distributed and compared with the T-test. In continues data, there are non-normally distributed, logarithmic transformation will be applied to approximate normal distribution as appropriate. Repeated measurements, mixed models will be made for analysis of the continuous variables with multiple measurements.

Missing data

In case of missingness greater than 5% for the primary endpoint, multiple imputations by chained equations will be applied as sensitivity analysis with generation of 10 individual data sets.

For other endpoints, first a worst case and best-case analysis will be made and if significant differences, multiple imputations will be performed.

Analysis of survival data and other outcomes

Kaplan-Meier curves for each group will be graphically displayed and compared by the log-rank test. Further multivariable Cox proportional hazard models will be applied to assess differences in time to death between treatment groups. These models will sequentially be adjusted for the interaction between treatment allocation, and each of the predefined covariates. Further, models stratified by individual components of the predefined covariates will be made as hypothesis generating. Any changes from the pre-specified analysis plan will be reported.

Outcomes will be evaluated using univariable and multivariable logistic regression models after examining assumptions of linearity and proportionality. Hazard ratios (HRs) and Odds ratios (ORs) with corresponding two-sided 95% confidence intervals (CI) will be presented.

Multivariable models are adjusted for:

*Admission SBP (quartiles), age, sex, body mass index, LVEF at admission (>50, 40-50, <40), NT-proBNP (above/below median), eGFR, supraventricular arrhythmia at admission, comorbidities (history of heart failure, obstructive pulmonary disease), systemic congested (Yes/no, defined as at least 3 kg above ideal weight at admission).*

The covariates are pre specified before analyses and were chosen based on a consensus of the steering committee based on experiences from previous trials of AHF. Interaction between covariates will be tested by adding the interaction term to the models.

Subgroup analysis

Subgroup analysis will be made for all the prespecified covariates. Interaction with treatment effect will be tested for each covariate and a forest plot will be plotted.

Two-sided p-value of less than 0.05 is considered statistically significant. All analyses will be conducted in the modified intention-to-treat (ITT) (all randomized patients fulfilling the inclusion criteria and excluding those, which consent have been withdrawn) population. Statistical analyses are performed using the SAS statistical software, version 9.4 (SAS Institute, Cary, NC) and in R version 3.3.3 (R Foundation for Statistical Computing, Vienna, Austria).

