# 7. Outcomes

## 7.1 Primary outcome

## Pulmonary parenchymal fluid content measured by ReDS after 24 hours preceded by 10 minutes without oxygen-supplementation.

## 7.2 Secondary outcomes

1. Arterial blood gas concentration after 24 hours preceded by 10 minutes without oxygen-supplementation.
2. All-cause mortality at day 30
3. Days alive out-of-hospital to day 30
4. Time to freedom from oxygen-supplementation

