# 8. Sample size calculations and statistical analysis plan

In a validation-trial of ReDS, Amir et al investigated 16 patients with acute heart failure and found a mean fluid content of 39.8 + 6.8 % [25]. Similar results were seen when estimating fluid content by the chest CT, which is regarded as the gold standard.

To have 90 % power to find a difference of 4 % in lung fluid content (change from 39.8% to 35.8%) with a standard deviation of 6.8, we need to include 122 patients (61 in each group). The α-level is 0.05, and the beta is 10%. We expect minimal dropouts. The study will include patients over an estimated period of 1 years in two centers. We will include patients until we have reached the estimated sample size without any missing values in the primary outcome, to ensure that we can conclude on our primary hypothesis.

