#### Remote Dielectric Sensing (ReDS)

Lung fluid content will be assessed noninvasively at admission and after 24 hours by the remote dielectric sensing (ReDS) device (Sensible Medical, Netanya, Israel). ReDS is an FDA-approved, wearable device developed by Sensible Medical Innovations that allows clinicians and other health care providers to quickly and accurately measure lung fluid in patients, noninvasively.

The lung fluid content is measured within the mid-region of the right lung. The measurement is presented as the percentage of the lung volume composed of fluid, (normal values for non-congested people is 20%-35% of fluid content) [25].

Using the ReDS technology in our study will seek to directly measure the degree of pulmonary congestion in acute heart failure patients and assess whether the effect of oxygen-level will be influenced by degree of pulmonary congestion at various points of care.

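### Section 12 does not fix one primary analysis for 24-hour ReDS, and baseline ReDS, though scheduled for all patients, is not among the named covariates

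*Protocol*

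**What the plan says.** Section 7.1 defines the primary outcome as a follow-up value, not a change: "Pulmonary parenchymal fluid content measured by ReDS after 24 hours preceded by 10 minutes without oxygen-supplementation". Section 9 schedules the same measurement twice: "Lung fluid content will be assessed noninvasively at admission and after 24 hours by the remote dielectric sensing (ReDS) device". The procedures table in Appendix 4 agrees, with ReDS marked before randomization and at 24 hours.

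Section 8 sizes the trial on a comparison of two means: "To have 90 % power to find a difference of 4 % in lung fluid content", "with a standard deviation of 6.8, we need to include 122 patients (61 in each group"). No correlation between baseline and 24-hour readings enters the calculation.

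Section 12 contains three statements that bear on the analysis:

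- Continuous variables are summarised as mean or median, log-transformed where suitable "if non-normally distributed and compared with the T-test". The rule is general and does not mention ReDS or the primary outcome.
- "Repeated measurements, mixed models will be made for analysis of the continuous variables with multiple measurements". No outcome, model structure or contrast is named.
- Under the subheading on survival data and other outcomes, after the Kaplan-Meier and Cox text: "Outcomes will be evaluated using univariable and multivariable logistic regression models after examining assumptions of linearity and proportionality". The results promised there are hazard ratios and odds ratios.

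The list of adjustment covariates covers systolic pressure, age, sex, body mass index, LVEF, NT-proBNP, eGFR, arrhythmia, comorbidities and systemic congestion. Section 12 says the list is pre-specified. Baseline ReDS is not on it.

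**The concern.** There are two related problems.

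First, the two-sided 0.05 threshold is not attached to one defined test of the primary outcome. The t-test and the mixed model can both be read as applying to 24-hour ReDS. They need not estimate with the same precision or give the same p-value. A choice between them that is left open until the data are in hand weakens the primary result.

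Second, the baseline reading of the same quantity is scheduled but has no stated place in the primary comparison. For any non-zero correlation between the two readings, adjusting for baseline narrows the confidence interval at no extra cost in patients. The adjusted models that Section 12 does name, Cox and logistic, do not yield an adjusted mean difference for a continuous percentage, and the covariate list leaves out the baseline value.

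**Working it through.** **Inputs.** Difference 4 points, SD 6.8, 61 per group, power 90%, alpha 0.05 (Section 8); two-sided testing (Section 12); 1:1 allocation (Section 4). The correlation r between baseline and 24-hour ReDS is not given. I assume r = 0.3 to 0.7, and the same SD of 6.8 at both times.

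**1. The plan's own figure.** n per group = 2 × [(1.960 + 1.282) × 6.8 / 4]² = 60.7, rounded up to 61, total 122. The stated number reproduces as an unadjusted two-sample comparison. Power at 61 per group is 90.1% by the normal approximation and 89.7% by the noncentral t.

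**2. Unadjusted t-test.** SE = 6.8 × √(2/61) = 1.231. With t(120) = 1.980, the 95% CI half-width is 1.980 × 1.231 = 2.44 points.

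**3. Linear model adjusted for baseline (ANCOVA).** Residual SD = 6.8 × √(1 − r²).

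**4. Comparison of change** (for example, a mixed model with unconstrained baseline means and a time-by-treatment contrast). SD of change = 6.8 × √(2(1 − r)).

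| Assumed r | t-test power | ANCOVA SD | ANCOVA SE | ANCOVA power | ANCOVA half-width | Change SD | Change power |
|---|---|---|---|---|---|---|---|
| 0.3 | 89.7% | 6.49 | 1.175 | 92.2% | 2.33 | 8.05 | 77.7% |
| 0.5 | 89.7% | 5.89 | 1.066 | 96.1% | 2.11 | 6.80 | 89.7% |
| 0.7 | 89.7% | 4.86 | 0.879 | 99.5% | 1.74 | 5.27 | 98.6% |

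All powers in the table are from the noncentral t, with 61 per group and a true difference of 4. At r = 0.5 the SD of change equals the raw SD, so the change analysis and the t-test have the same power. Below that the change analysis is weaker, and above it stronger. ANCOVA has the highest power of the three at each r shown.

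**5. Chance baseline imbalance.** The SE of the baseline difference between groups is also 6.8 × √(2/61) = 1.23 points. With equal SDs, only r times a chance gap is expected to carry into the 24-hour difference. For a gap of 1.2 points that is 0.36, 0.60 or 0.84 points at r = 0.3, 0.5 or 0.7, which is 9%, 15% or 21% of the 4-point target.

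**The case against.** The strongest reply is that nothing is broken. Under randomisation the t-test is unbiased, its standard error already allows for chance baseline imbalance, and it agrees with the sample size. That stands: the case for adjustment is one of efficiency. At r = 0.3 the gain is modest, 2.5 percentage points of power and 0.11 points of half-width.

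The size of the gain also rests on a correlation the protocol does not give. The two readings are taken under different conditions: oxygen may be given freely before randomisation (Section 5.1), whereas the 24-hour reading follows 10 minutes without it. This could lower r. It is a reason to show a range, as above, and not a reason to leave the baseline out.

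A reader might infer more than the protocol supports, in three ways:

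- *That baseline ReDS is never used.* The mixed-model sentence covers ReDS by its wording and could bring the baseline reading in. Section 9 also foresees examining whether the oxygen effect depends on the degree of congestion.
- *That the primary outcome will be analysed by logistic regression.* The sentence stands with the survival analyses and leads to hazard and odds ratios, so event outcomes are its natural reading. No cut-point for ReDS is given. Its word for outcomes is unrestricted, which is worth tidying, but dichotomising ReDS is not established.
- *That every patient will have a baseline reading.* The protocol schedules one for all. The promise in Section 8 of no missing values concerns the primary outcome only.

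Finally, a separate analysis plan or the planned design paper might settle the model. But Section 12 is itself presented as the statistical analysis plan and calls its covariates pre-specified, so the ambiguity and the omission are in text that purports to be fixed.

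**Conclusion.** The point holds as a matter of an unfixed primary analysis and forgone precision. Section 12 leaves the t-test and an unspecified mixed model both open for 24-hour ReDS, names no linear adjusted model, and omits baseline ReDS from its covariate list.

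On the assumptions of equal SDs and r between 0.3 and 0.7, the permitted readings range from 77.7% power (change, r = 0.3) through 89.7% (t-test) to 98.6% (change, r = 0.7). A baseline-adjusted linear model has 92.2% to 99.5%, and its interval is narrower than that of the t-test by 0.11 to 0.70 points of half-width (2.44 against 2.33 and 1.74). The documents do not support calling the planned t-test invalid or the trial underpowered on its own assumptions. This should be changed, but the trial could be interpreted without it if the t-test were clearly declared primary.

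**What to change.** In Section 12, name one primary analysis: a linear model (ANCOVA) of 24-hour ReDS on allocation, with baseline ReDS as a continuous covariate, reporting the adjusted mean difference with its 95% CI and two-sided p-value. Add a simple rule that keeps patients with a missing baseline reading in the analysis, for example mean imputation of the baseline covariate. Keep the unadjusted t-test as a sensitivity analysis. State that the logistic models apply to binary outcomes, and say which outcomes the mixed models are for.

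The cost is a few sentences before unblinding. No new measurements or patients are needed, and the sample size of 122 can stay as it is.

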## 13.5 Reporting

At each assessment of an AE/AR, it must be evaluated if it should be categorized as a serious adverse event/ (SAE), and if so, this must be reported to the trial sponsor. The trial sponsor will evaluate all SAE/SAR.

Death resulting from circulatory collapse will be recorded but will not be reported to the ethical committee outside the annual reports, as AHF patients have a ≥20% risk of death within 30 days. The death rate will have no essential information in the monitoring of trial by authorities.

All SAEs occurring at the trial centers will be submitted once a year by the sponsor and a safety report of all trial patients will be submitted to the ethical committee.

No later than 90 days after the trial has been completed, the trial sponsor will notify the ethical committee, and if the trial is stopped earlier than planned, the reasons will be reported.

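### The adjusted mortality models carry 15 to 18 parameters on about 24 deaths, so the planned adjusted hazard and odds ratios would be moderately exaggerated, with intervals somewhat too narrow

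*Protocol*

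**What the plan says.** Protocol section 12, Statistical analyses plan, compares survival by Kaplan-Meier curves and a log-rank test, and then adds: "Further multivariable Cox proportional hazard models will be applied to assess differences in time to death between treatment groups". The next sentence reads: "These models will sequentially be adjusted for the interaction between treatment allocation, and each of the predefined covariates". Univariable and multivariable logistic models are also planned, and hazard and odds ratios with 95% confidence intervals are to be presented.

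One list of covariates serves every multivariable model. It opens with "Admission SBP (quartiles), age, sex, body mass index, LVEF at admission (>50, 40-50, <40), NT-proBNP (above/below median), eGFR" and goes on to supraventricular arrhythmia, history of heart failure, obstructive pulmonary disease and systemic congestion. The section describes the list as fixed before analysis. It also plans tests of interaction between covariates and, under subgroup analysis, a test of interaction with treatment for each covariate, shown in a forest plot.

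All-cause mortality at day 30 is a secondary outcome (section 7.2). The 122 patients were sized on lung fluid content alone (section 8). The only mortality figure in the protocol is in section 13.5, Reporting: "AHF patients have a ≥20% risk of death within 30 days".

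**The concern.** A covariate list that suits a continuous outcome in 122 patients is also fixed for an outcome whose information is limited by the number of deaths. With very few deaths per parameter, maximum likelihood pushes coefficients away from zero and reports standard errors that are too small. When a category contains no deaths, a coefficient cannot be estimated at all.

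The sentence on interactions raises a second problem. If a treatment-by-covariate term enters a model meant to compare the groups, the treatment coefficient becomes the effect at the covariate's reference value and no longer the overall effect.

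At stake is the reporting of a named secondary outcome. A significant adjusted hazard ratio could stand beside a null log-rank test, and the protocol does not say which of the two decides.

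**Working it through.** **1. Sample size reproduced.** Inputs from section 8: difference 4, SD 6.8, α 0.05 (two-sided by section 12), power 90%. Per arm: 2 × (1.960 + 1.282)² × 6.8² / 4² = 60.7, so 61 per arm and 122 in all. This agrees with the protocol. Mortality plays no part in it.

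**2. Parameters.** SBP quartiles 3, LVEF classes 2, and one each for age, sex, body mass index, NT-proBNP, eGFR, arrhythmia, heart failure history, obstructive pulmonary disease and congestion: 3 + 2 + 9 = 14. Treatment makes 15. This takes continuous covariates as linear. Interactions enter one covariate at a time and add 1 to 3 terms, so a single model then has 16 to 18.

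**3. Deaths per parameter** (122 × mortality, divided by the number of parameters).

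| 30-day mortality | Deaths | Per 15 | Per 18 |
|---|---|---|---|
| 10% (assumed) | 12.2 | 0.8 | 0.7 |
| 20% (protocol's lower bound) | 24.4 | 1.6 | 1.4 |
| 25% (assumed) | 30.5 | 2.0 | 1.7 |
| 30% (assumed) | 36.6 | 2.4 | 2.0 |

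**4. Consequence at about 24 deaths.** The protocol gives no covariate prevalences or effects. Trials of 122 patients were therefore simulated under several assumed sets, with 400 to 1,500 trials per scenario where the number is recorded. The ranges below run across those sets.

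| Quantity | 15-parameter Cox | Treatment-only Cox |
|---|---|---|
| Reported SE of log HR | 0.47–0.50 | 0.41–0.43 |
| True SD of log HR | 0.52–0.60 | 0.43–0.48 |
| Mean estimate, true HR 0.50 | 0.41–0.44 | 0.49–0.51 |
| False positives at nominal 5% | 6.3–9.5% | 4.0–6.0% |
| Coverage of 95% interval | 93–94% | not recorded |
| Trials with a non-estimable coefficient | about 2–4% | – |
| Same, with treatment × SBP quartile added | 35–46% | – |

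- On the log scale, an HR of 0.44 against 0.50 is a bias of ln(0.50) − ln(0.44) = 0.13, and 0.41 is a bias of 0.20. That is roughly a quarter to two fifths of one standard error. The comparison is with the hazard ratio used to generate the data.
- With 400 trials, the Monte Carlo error of a false-positive rate near 6 to 9% is 1.2 to 1.5 points. The 1,500-trial set gave 7.0% against 4.3% unadjusted, with an error of √(0.07 × 0.93 / 1500) = 0.7 points.
- The SD of 0.60 comes from a set in which the treatment-only model also showed a gap (0.48 against 0.41). Not all of that difference is due to the long covariate list.
- The 15-parameter logistic model behaved similarly. The SD of the log odds ratio was 0.74 against a reported SE of 0.58 with no effect, and 0.68 against 0.61 with HR 0.50.

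**5. Why the quartile interaction fails.** Four quartiles in two arms make 8 cells of 122/8 = 15.25 patients, with 24.4/8 = 3.05 deaths each. At a uniform 20% risk, the chance of no death in a given cell is 0.8^15.25 = 0.033. The chance that at least one of the 8 is empty is about 1 − 0.967⁸ = 0.24, before any other covariate enters.

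**6. Meaning of the coefficient.** With log hazard = βT + γA + δTA, the treatment log HR at covariate value A is β + δA. β alone is the effect at A = 0. For uncentred age this is age zero; for SBP it is the reference quartile, with about 24.4/4 = 6 deaths.

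**7. Other mortality rates.** At 25%, main-effects failures fell to 1–2% and interaction failures to 19–24%. At 30%, no main-effects fit failed. At an assumed 10%, 23% of main-effects fits failed with no effect and about 49% with HR 0.50.

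**The case against.** The strongest reply is that the adjusted models are only supportive. The log-rank test comes first, univariable logistic models are planned, and mortality is one of four secondary outcomes in a self-described pilot. No primary conclusion depends on these models. The bias is modest beside a standard error of about 0.5, and coverage stays at 93 to 94%. Details such as penalisation belong in a statistical analysis plan that may exist. Most of this stands and limits the weight of the point. It does not remove it: the covariate list and the models are stated choices, not gaps, and the protocol does not say which mortality analysis is the main one.

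A reader might infer more than the documents support:

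- **That mortality is tested only in overfitted models.** It is not, because unadjusted comparisons are planned and remain valid.
- **That 24 deaths is an upper limit.** The protocol's figure is a lower bound on risk, so 24 is its floor. Fewer deaths are plausible, since hypotensive patients are excluded (section 6.4) and consent comes from the patient (section 9.2), but that is an assumption.
- **That the main-effects models commonly fail.** At 24 deaths they rarely do. The high failure rates need a mortality well below the protocol's.
- **That an effect at age zero will be reported as the treatment effect.** Nothing says so. The subgroup paragraph describes ordinary interaction tests with a forest plot, so the sentence on sequential adjustment is a wording risk.

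Cutting SBP at quartiles and NT-proBNP at the median in models of continuous outcomes is a matter of preference and forms no part of this point.

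**Conclusion.** The point holds at moderate size. On the protocol's own figures, the adjusted mortality models have about 1.6 deaths per parameter, and still only 2.4 at 30% mortality. This needs no outside assumption beyond linear continuous terms.

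The consequences rest on assumed covariate distributions, but all the simulated sets agree in direction. A true hazard ratio of 0.50 is estimated at about 0.41 to 0.44, reported standard errors fall short of the true spread, and false positives exceed those of the treatment-only model. Main-effects fits fail only occasionally. Serious failure at 24 deaths lies in the SBP-quartile interaction models, where roughly 35 to 45% have a non-estimable coefficient.

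The unadjusted mortality comparison and the primary outcome are unaffected. The change should be made because the outcome is a named one and the repair is wording only.

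**What to change.** For 30-day mortality, amend section 12, Statistical analyses plan, as follows:

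1. Name the unadjusted analysis as the main one: the Kaplan-Meier difference in 30-day risk with its 95% confidence interval, the log-rank test, and a Cox hazard ratio with treatment as the only term.
2. Limit any adjusted Cox or logistic model for mortality to one or two covariates named in advance. With one parameter each, this gives 24.4/2 = 12.2 or 24.4/3 = 8.1 deaths per parameter. If more covariates are kept, use Firth penalisation.
3. Reword the sentence on sequential adjustment. For example: *Models with a treatment-by-covariate interaction serve only the interaction tests and the forest plot; the overall treatment effect is not taken from them.*

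The full covariate list can stay for continuous outcomes. The change affects analysis text only: no patient, visit or measurement changes. The downside is less covariate adjustment for mortality, which about 24 deaths cannot support. The change does not add power: with 24.4 deaths, even the unadjusted test has about 40% power for a hazard ratio of 0.50 (√24.4/2 × 0.693 − 1.96 = −0.25, and Φ(−0.25) = 0.40).

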# 4. Study design

The study is an investigator-initiated, prospective, randomized, blinded, multi-center, controlled trial. Following successful completion of screening procedures, patients will be randomized in a 1:1 fashion to receive either of the 2 treatments-strategies.

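### The Cox models for time to death carry treatment-by-covariate interactions, and the protocol does not say that the treatment hazard ratio comes from a model without them

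*Protocol*

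**What the plan says.** Under the heading on survival data in Section 12, the protocol compares Kaplan-Meier curves by the log-rank test and then gives the Cox models their purpose: "Further multivariable Cox proportional hazard models will be applied to assess differences in time to death between treatment groups". The next sentence concerns the same models: "These models will sequentially be adjusted for the interaction between treatment allocation, and each of the predefined covariates". Only the stratified models in the sentence after that are labelled hypothesis generating.

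The section promises hazard ratios with two-sided 95% confidence intervals and lists eleven adjustment covariates. Age, BMI and eGFR have no categories and no centring. The other eight are categorical, among them systolic blood pressure in quartiles and NT-proBNP split at the median.

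The subgroup paragraph of the same section provides separately for effect modification: "Interaction with treatment effect will be tested for each covariate and a forest plot will be plotted".

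**The concern.** In a model with treatment, a covariate and their product, the treatment coefficient is the log HR where the covariate equals zero, or in its reference category. That is a different quantity from the difference between arms, which is the stated purpose of these models. In a randomised comparison there is no reason to adjust the treatment effect for its own interaction with a baseline variable, and the subgroup paragraph already covers effect modification.

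Three details of wording make the literal reading plausible. The sentence refers back to the models that compare the arms. It speaks of adjusting, the verb also used for the covariate list, where the subgroup paragraph speaks of testing. And if it meant only testing, it would repeat the subgroup paragraph.

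The multivariable Cox models are the only named source of an HR for mortality. Eleven covariates entered one at a time could give eleven different treatment coefficients, with no rule for which is the result. Section 14 relies on the primary and secondary outcomes for the balance of benefit and harm, and day-30 mortality is a secondary outcome. A very wide interval around a misread HR could be taken as absence of harm.

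**Working it through.** **Inputs from the protocol**
- Significance level, Section 8: "The α-level is 0.05, and the beta is 10" (beta in per cent). Sidedness, Section 12: "Two-sided p-value of less than 0.05 is considered statistically significant".
- Basis of the sample size, Section 8: "To have 90 % power to find a difference of 4 % in lung fluid content (change from 39.8% to 35.8%) with a standard deviation of 6.8". The same section gives the resulting size as 61 per arm, 122 in total.
- Allocation, Section 4: 1:1.
- 30-day risk of death, Section 13.5: at least 20%. This gives 0.20 × 122 = 24.4, taken as 24 deaths.

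**Assumed, not in the protocol:** the HRs; 20% mortality over both arms together; age mean/SD from 70/12 to 78/9; BMI 27/6; eGFR 55/22; a reference category holding 80% of patients as an example of an unequal split.

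**1. The plan's own figure.** n per arm = 2(1.960 + 1.282)² × 6.8² / 4² = 60.7, rounded up to 61, so 122 in total, with 90.1% power. The stated size is reproduced. It concerns lung fluid content only; no power or number of deaths is stated for mortality.

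**2. Treatment term without an interaction.** SE(log HR) = 2/√24 = 0.408. At HR 0.5, z = 0.693/0.408 = 1.698. Power = Φ(1.698 − 1.960) + Φ(−1.698 − 1.960) = 40%. At HR 0.3 it is 84%.

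**3. Treatment term with an interaction.** The variance is multiplied by about 1 + (mean/SD)² for an uncentred continuous covariate, and by 1/(share of patients in the reference category) for a categorical one. For age 75/10 the factor is 1 + 7.5² = 57.25, so the SE is 0.408 × √57.25 = 3.09, z = 0.224 at HR 0.5, and power is 5.6%.

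| Covariate in the product term | Variance factor | Power, HR 0.5 | Power, HR 0.3 |
|---|---|---|---|
| None | 1 | 40% | 84% |
| Age, uncentred (70/12 to 78/9) | 35 to 76 | 5–6% | 6–8% |
| BMI, uncentred (27/6) | 21 | 7% | 10% |
| eGFR, uncentred (55/22) | 7.25 | 10% | 20% |
| Blood-pressure quartiles | 4 | 14% | 31% |
| NT-proBNP median split | 2 | 22.5% | 55% |
| Reference category of 80% | 1.25 | 33% | 75% |

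**4. Simulation check.** 400 trials per HR, 122 patients, on average 25 to 28 deaths by day 30, no true interaction:

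| Model from which the treatment term is read | HR 0.5 | HR 0.3 |
|---|---|---|
| Treatment only | 37% | 85% |
| Treatment and age | 39% | 86% |
| Treatment × age, uncentred | 8% | 7% |
| Treatment × age, centred | 36% | 83% |
| Treatment × median split | 14% | 48% |
| Treatment × quartiles | 4% | 13% |

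The simulation agrees with the formula in direction. It gives lower power than the formula for the categorical covariates, most of all for quartiles, where the reference cell often holds very few deaths and the Wald test is unstable. With age centred, almost all the power returns. The loss therefore comes from the coding of the covariate and from which term is read, not from the mere presence of a product term.

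**The case against.** The protocol never names the treatment coefficient of an interaction model as its test. Adding interactions sequentially can mean that a main-effects model is fitted first and product terms enter one by one. The covariate list contains no product terms, and the text on interactions between covariates speaks of adding a term to existing models. Centring and coding are details that an analysis plan commonly settles. The covariate distributions and HRs used above are assumptions, and power for death is low in any case, since the trial is sized on lung fluid content.

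Most of this stands and limits the point. A reader might infer that the trial loses nearly all its power to detect a mortality difference, or that no planned analysis estimates that difference. The documents do not support either. The log-rank test compares the arms directly. Day-30 mortality can also be compared by the chi-squared or Fisher's exact test and by univariable logistic regression, none of which involves these interactions. Near-total loss applies to three of the eleven covariates, and only if they are uncentred.

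The objection does not remove the ambiguity. The text states no main-effects step and no contrast for the Cox result, and its literal wording attaches the interactions to the models that compare the arms. The log-rank test gives a p-value but not the promised HR and interval.

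**Conclusion.** The point holds as a defect in the specification of the Cox HR for one secondary outcome. What the treatment coefficient means in an interaction model is a matter of algebra and rests on no assumption. The size does rest on assumptions: 24 deaths, an HR of 0.5 and typical covariate distributions. More deaths would raise every power figure but leave the variance factors unchanged. It cannot be said that the analysts will read the wrong term, only that the wording permits it and points that way. The between-arm significance test for survival is intact. Low power for mortality is a separate matter that this change does not cure: at HR 0.5, 80% power would need 66 deaths. The sentence should be corrected before analysis.

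**What to change.** Remove the interaction sentence from the Cox paragraph in Section 12. State that the treatment HR, 95% CI and p-value for time to death come from the Cox model with treatment and covariate main effects only. Fit treatment-by-covariate terms only for the subgroup analysis, and report there the interaction test and the treatment effect within each level, or at stated values of age, BMI and eGFR. Do not report the treatment main-effect coefficient from those models as a between-arm result.

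The cost is a small change of wording and fewer models to run. No patients or data are needed, and no analysis is lost, because the subgroup paragraph already covers effect modification.
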